## Abstract

**Introduction:**

Liver transplantation is a complex operation that can provide significant improvements in quality of life and survival to the recipients. However, serious complications are common and include major haemorrhage, hypotension and renal failure. Blood transfusion and the development of acute kidney injury lead to both short-term and long-term poor patient outcomes, including an increased risk of death, graft failure, length of stay and reduced quality of life. Octreotide may reduce the incidence of renal dysfunction, perioperative haemorrhage and enhance intraoperative blood pressure. However, octreotide does have risks, including resistant bradycardia, hyperglycaemia and hypoglycaemia and QT prolongation. Hence, a randomised controlled trial of octreotide during liver transplantation is needed to determine the cost-efficacy and safety of its use; this study represents a feasibility study prior to this trial.

**Methods and analysis:**

We describe a multicentre, double-blind, randomised, placebo-controlled feasibility study of continuous infusion of octreotide during liver transplantation surgery. We will recruit 30 adult patients at two liver transplant centres. A blinded infusion during surgery will be administered in a 2:1 ratio of octreotide:placebo. The primary outcomes will determine the feasibility of this study design. These include the recruitment ratio, correct administration of blinded study intervention, adverse event rates, patient and clinician enrolment refusal and completion of data collection. Secondary outcome measures of efficacy and safety will help shape future trials by assessing potential primary outcome measures and monitoring safety end points. No formal statistical tests are planned. This manuscript represents study protocol number 1.3, dated 2 June 2021.

**Ethics and dissemination:**

This study has received Research Ethics Committee approval. The main study outcomes will be submitted to an open-access journal.

**Trial registration:**

The study is registered with ClinicalTrials.gov (NCT04941911) with recruitment due to start in August 2021 with anticipated completion in July 2022.

**Clinical trials unit:**

Surgical and Interventional Group, Division of Surgery & Interventional Science, University College London.

Strengths and limitations of this studyThis study is prospective, randomised and designed to minimise the risk of bias throughout.We have prioritised patient input throughout the development and design of this study.A small sample size has been selected to demonstrate feasibility end points as a precursor to a larger efficacy and safety trial.The secondary end points will provide clinically relevant data on which to design this cost effectiveness study.

## Introduction

Liver transplantation is a potentially life transforming intervention with excellent outcomes (1-year and 5-year survival of 94% and 84%, respectively).^1^ It is, however, a major operation in patients with multiple comorbidities and is associated with a 3% perioperative mortality rate and 70% complication rate. Intraoperative haemorrhage is serious and commonly occurs during mobilisation of the diseased liver, exacerbated by coagulopathy and abnormal vasculature due to portal hypertension. Bleeding can cause hypotension, reduced perfusion of the transplanted graft and increased incidence of acute kidney injury (AKI). Blood loss and transfusion are associated with increased morbidity, mortality and cost of transplantation and can have a long-term detrimental effect on patient well-being and quality of life.^2–4^

Octreotide is a synthetic analogue of somatostatin with an excellent safety profile^5^ that may improve renal outcomes, reduce perioperative bleeding and increase exogenous vasopressor sensitivity during liver transplantation. AKI following liver transplantation occurs in 25%–60% of patients with normal renal function prior to surgery, with half of these patients requiring renal replacement therapy (RRT) after surgery.^6 7^ The need for post-transplant RRT increases the length of hospital stay and the risk of early allograft dysfunction, chronic kidney disease (CKD) and mortality.^8 9^ Risk factors for renal dysfunction following transplantation include intraoperative hypotension, lower quality donor grafts, hepatic ischaemia-reperfusion injury, blood transfusion and preoperative renal disease.^10 11^ Octreotide has been shown to enhance renal blood flow, glomerular filtration and urine output in decompensated liver cirrhosis,^12^ hepatorenal syndrome^13^ and may also reduce the incidence of post-transplant renal injury.^14 15^

Major haemorrhage and transfusion during and after liver transplantation reduce patient and graft survival as well as increasing length of stay and the need for RRT.^2–4 16–18^ Haemorrhage risk during liver transplantation is multifactorial, including cirrhotic coagulopathy, portal hypertension and hyperfibrinolysis. Bleeding is driven by the presence of widespread dilated collaterals and a hyperdynamic splanchnic circulation. Octreotide causes splanchnic vasoconstriction thereby reducing splanchnic blood flow, collateralisation and portal venous pressures which may reduce surgical blood loss.^19^ This correction of the abnormal blood distribution and venous pooling increases systemic blood pressure^20^ and, when combined with a vasopressor, correlates with improved renal function.^21^ Furthermore, increased systemic pressures and vasopressor sensitivity help preserve renal function and reduce myocardial injury.^10 22 23^

### Previous clinical studies of octreotide in liver transplantation

A retrospective cohort study of octreotide infusion during liver transplantation demonstrated a reduction in transfusion requirement by 2.3 units of packed red blood cells but this difference was not statistically significant.^24^ A randomised controlled trial (RCT) of octreotide infusion during liver transplantation found an enhancement of norepinephrine effect on blood pressure with a mean increase of 8 mm Hg.^15^

#### Risks

Octreotide is not currently licensed for use in liver transplantation. Common risks of octreotide include changes in blood sugar levels, heart rate and rhythm. The side effect profile of octreotide during liver transplantation is unknown. The studies to date did not compare safety or adverse events between the octreotide and placebo arms,^15^ have not been fully published^25^ or did not assess adverse events.^24^

#### Rationale for this study

The background literature for the use of octreotide in liver transplantation is inconclusive and the current use in this setting is clinician and institution dependent. While there is reasonable evidence to support its use in this setting, octreotide has harmful effects which need to be considered against its efficacy and cost. Furthermore, patients may be unwilling to have non-essential medication and clinicians may not support its use in all transplant settings. In addition to determining the feasibility of a multisite drug trial in liver transplantation, secondary end points will provide clinically relevant data on which to design a subsequent cost-effectiveness study.

### Hypothesis

It is feasible to recruit and retain patients in a randomised study of continuous infusion of octreotide during liver transplantation surgery.

## Methods and analysis

### Trial design

The purpose of this study is to determine the feasibility of recruiting patients to a double-blind, randomised, placebo-controlled trial of intravenous octreotide during liver transplantation. We will recruit 30 adult patients at two liver transplant centres; The Royal Free London NHS Foundation Trust (Royal Free Hospital, RFH; National Health Service, NHS), and University Hospitals Birmingham NHS Foundation Trust (University Hospital Birmingham). A blinded infusion will be administered during transplantation surgery. Patients will be allocated in a 2:1 ratio to octreotide or placebo. All members of the research, anaesthetic, surgical, intensive care and nursing teams will be blinded to patient allocation; this includes all outcome assessors and data analysts. Patients will be blinded to their allocation and will have the option to find out which intervention they received after the study is complete. Unblinding will be carried out once data cleaning and analysis has been completed.

This protocol conforms to the Standard Protocol Items: Recommendations for Interventional Trials.^26^ The RCT will be reported in line with the Consolidated Standards of Reporting Trials statement.^27^ This trial is non-commercial and does not intend to generate data for drug licensing. The study is registered with ClinicalTrials.gov (NCT04941911) with recruitment due to start in August 2021 with anticipated completion in July 2022. WHO Trial Registration Data Set in table 1.

**Table 1 T1:** WHO trial registration data set

Data category	Information
Primary registry and trial identifying number	ClinicalTrials.gov NCT04941911
Date of registration in primary registry	28 June 2021
Source(s) of monetary or material support	National Institute of Health Research
Primary sponsor	University College London, UK
Contact for public queries	MS ([contact])
Contact for scientific queries	MS ([contact])
Public title	A feasibility study of octreotide infusion during liver transplant
Scientific title	A double-blind randomised placebo-controlled feasibility study to assess the impact of octreotide infusion during liver transplantation on post-operative renal failure
Countries of recruitment	UK
Health condition(s) or problem(s) studied	Liver transplantation
Intervention(s)	Active comparator: intravenous octreotide acetate infusion, 100 mcg bolus with a subsequent infusion of 100 mcg per hour during surgery
	Placebo comparator: sodium chloride 0.9% w/v
Key inclusion and exclusion criteria	Ages eligible for study: ≥18 years Sexes eligible for study: both Accepts healthy volunteers: no
	Inclusion criteria: adults aged 18 years and over undergoing primary liver transplantation of a whole or partial liver graft from a cardiac or brain dead donor
	Exclusion criteria: previous solid organ transplant, acute liver failure, fulminant hepatic failure, patients receiving a living donor liver graft, patients currently admitted to ICU prior to transplantation, requirement of haemodialysis or continuous veno-venous haemofiltration (CVVHF) preoperatively, known allergy or adverse reaction to octreotide, preoperative decision to use intra-operative CVVHF, a positive pregnancy test.
Study type	Interventional
	Allocation: patients will be randomised in a 2:1 ratio to either octreotide or placebo groups. Stratified randomisation of patients by source of liver graft (brain death or cardiac death). Masking: quadruple (participant, care provider, investigator, outcomes assessor)
	Primary purpose: feasibility
	Phase II
Date of first enrolment	July 2021
Target sample size	30
Recruitment status	Pending recruitment
Primary outcome(s)	Trial feasibility
Key secondary outcomes	Incidence of acute kidney injury Postoperative incidence of a new requirement for renal replacement therapy Incidence of new chronic kidney disease or deterioration of chronic kidney disease Incidence of early allograft dysfunction Patient mortality Intra-operative red blood cell salvage Volume of packed red blood cell transfusion administered Incidence of adverse events secondary to study drug infusion PROMs data

ICU, intensive care unit; PROMs, patient recorded outcome measures.

### Eligibility

#### Inclusion criteria

Adults aged 18 years and over accepted for liver transplant and on the transplant waiting list.Undergoing liver transplantation.Recipient of a whole or partial liver graft from a cardiac or brain dead donor.

#### Exclusion criteria

Lacking capacity to provide consent (according to the Mental Capacity Act, 2005).Recipients of multiple solid organ transplants.Previous receipt of a solid organ transplant.Patients with acute or fulminant hepatic failure.Patients receiving a live-donor liver graft.Patients admitted to an intensive care unit (ICU) at the time of transplantation.Preoperative requirement for RRT, including dialysis.Known allergy or adverse reaction to octreotide.Preoperative decision to use intraoperative RRT.Patients enrolled in another interventional study that affects patient care during transplantation surgery or would be expected to have an effect on the study outcomes will be excluded from this study.

Patients who are enrolled in a study examining the impact of extracorporeal machine perfusion of the donated liver prior to transplantation will be eligible for this study.

### Patient identification and recruitment

Participant screening and registration will be undertaken locally at each study site. Overall trial flow is outlined in online supplemental appendix 1.

10.1136/bmjopen-2021-055864.supp1Supplementary data

Patients will be identified and recruited in two ways, depending on whether they are undergoing assessment for suitability for liver transplantation or have already been accepted onto the waiting list for transplantation. Screening will be performed by the clinical team, as will primary contact regarding engagement with research, prior to research team contact.

i. Patients undergoing assessment for liver transplantation will be sent the patient information sheet (PIS) for this study. Patients that meet the inclusion criteria will be approached during their in-patient assessment process to explain the study and for preliminary informed consent.

ii. Patients already listed for liver transplantation who meet the inclusion criteria will be sent the PIS. These patients will be contacted by phone, the study and PIS explained, and preliminary informed consent taken.

Due to the waiting time for transplant and the fixed duration of this study many patients who would be willing to enter the study will not be able to participate because a donor organ does not become available. Both groups of patients will therefore have their consent confirmed on the day of admission for surgery at which point, once the transplant surgery has been confirmed, the patient will be considered to be enrolled.

#### Consent

Informed consent will be obtained by a member of the research team and confirmed when the patient is admitted for surgery. The PIS and consent form (online supplemental appendices 2 and 3) will be reviewed and updated, if necessary, throughout the trial (eg, where new safety information becomes available). Consent will be sought for use of participant data in further studies in relation to this research.

10.1136/bmjopen-2021-055864.supp2Supplementary data

10.1136/bmjopen-2021-055864.supp3Supplementary data

### Study interventions

Patients will follow the standard protocol for liver transplantation at each study centre with the only study intervention being the provision of octreotide or placebo infusion. The study infusion will commence after induction of anaesthesia and prior to surgical incision. There will be no cross-over or dose escalation. The study infusate will be administered intravenously through an electronic infusion pump until completion of 50 mL of study medication or transfer to ICU, whichever is sooner. The maximum total dose of octreotide infused will be 1 mg, including an initial slow bolus followed by an infusion. Similarly, the maximum dose of 0.9% saline placebo administrated will be 50 mL. Where the infusion is completed prior to the end of surgery then no further study drug or placebo will be given.

#### Intervention group

Syringes will contain 50 mL of octreotide acetate at 20 mcg/mL in 0.9% w/v sodium chloride in water.

The octreotide infusion will commence with a 100 mcg bolus (5 mL) over 30 min with a subsequent infusion of 100 mcg (5 mL) per hour during surgery.

#### Comparator group

Syringes will contain 50 mL of 0.9% w/v sodium chloride in water.

The control infusion will commence with a 5 mL bolus over 30 min with a subsequent infusion of 5 mL per hour during surgery.

#### Study drug

Octreotide is licensed in the UK and is being used outside of its marketed authorisation for the purpose of this trial. The Summary of Product Characteristics will be used as a safety reference and the dose will not exceed the maximum dose of 1.5 mg/day. A suitable marketed product will be sourced by the RFH Pharmacy Manufacturing Unit that allows 7 days stability after reconstitution. The study drug will be prepared and released by a Qualified Person for use in the study by the holder of a Manufacturing and Import Authorisation (Investigational Medicinal Products) licence.

#### Overdose

Deviations from the treatment schedule or inadvertent administration of additional octreotide may lead to overdose. These will be reported in the case report form (CRF), the patient will be notified and the information and implications reported to the Sponsor. The patient would continue to be included in the trial. Where a serious adverse event (SAE) occurs in association with an overdose then the nature, dose and cause of the overdose will be included in an SAE report form. Participants who receive an overdose of octreotide will be followed up and treated in the usual manner for the trial.

Relevant symptoms of overdose include arrhythmia, hypotension, cardiac arrest, pancreatitis, hepatic steatosis, diarrhoea and lactic acidosis. Management is supportive.

### Randomisation

Consented patients who proceed to transplantation will be randomised. Remote-site computerised random allocation will be performed with a centrally generated code (www.sealedenvelope.com) that will correlate with a coded syringe held in the secure study drug storage facility at each study centre. Patients will be stratified within the randomisation process by source of liver graft (brain death, DBD, or cardiac death donor, DCD) to ensure that patients are balanced for these factors across the two treatment groups. Patients will be randomly allocated to either the octreotide or placebo study groups in a 2:1 ratio. The randomisation list will be held centrally at a dedicated and independent off-site facility that will be contactable 24 hours a day.

### Allocation concealment

The syringes of octreotide 20 mcg/mL (intervention) and sodium chloride 0.9% w/v (control) will appear identical and only identifiable by their trial-allocated code. No members of the research or clinical team will be aware of patient allocation or syringe contents. The allocation code will only be broken following completion of patient follow-up, data cleaning and analysis; unless an emergency break code is requested. The study statistician will be provided only with information on treatment A or B.

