### Sample size

Thirty patients will be recruited from two sites, with 20 in the study drug (octreotide) arm and 10 in the placebo. This sample will allow us to demonstrate the feasibility of conducting a full-scale randomised trial. This study is not powered to detect differences in treatment effect but will obtain estimates of an effect and its variance.^30^ This sample size will allow us to estimate patient consent rate with a 95% CI of ± 10% (based on 100 participants approached). The secondary outcome data will provide the required information for a sample size calculation for the primary end point of a subsequent trial.^31^ Survival to discharge is above 96% for both study sites and hence it is likely that the ninety day follow data collection will be achieved for the majority of patients.

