#### Secondary outcomes

Numerical outcomes will be summarised using either mean (SD) or medians (IQR) as appropriate. Binary and ordinal outcomes will be summarised using number (%). The degree of precision will be quantified using 95% CIs. Differences between groups will be quantified using differences in means or proportions, as appropriate with corresponding 95% CIs.

Since this is a feasibility study, no formal statistical tests are planned.

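### With 2:1 allocation and planned arms of 20 and 10, A/B labels alone do not keep the statistician blinded during the analysis

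*Protocol article*

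**What the plan says.** All references are to the protocol article.

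- **Who is blinded.** Trial design lists the teams that will not know the allocation and adds that "this includes all outcome assessors and data analysts".
- **Until when.** The same section says: "Unblinding will be carried out once data cleaning and analysis has been completed". Allocation concealment agrees: "The allocation code will only be broken following completion of patient follow-up, data cleaning and analysis; unless an emergency break code is requested".
- **By what means.** For the statistician, Allocation concealment gives one device: "The study statistician will be provided only with information on treatment A or B".
- **Arm sizes.** Randomisation states: "Patients will be randomly allocated to either the octreotide or placebo study groups in a 2:1 ratio". Sample size gives the numbers: "Thirty patients will be recruited from two sites, with 20 in the study drug (octreotide) arm and 10 in the placebo".
- **Analysis set.** Statistical methods analyses patients in their randomised groups, and Patient replacement says that those who do not complete are not replaced. The labelled groups therefore keep their randomised sizes.

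No section describes a step that would hide group size, such as splitting the larger arm into two codes or writing the analysis on dummy allocations.

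**The concern.** A two-letter code hides the arms only if nothing else in the dataset tells the letters apart. With equal allocation, group size tells the reader nothing. With 2:1 allocation and a published ratio, it tells almost everything: the first frequency table by label shows one group about twice the size of the other. The article nevertheless relies on the code up to the end of the analysis.

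At stake is a stated protection that the design does not deliver at the stage where it is claimed. The comparative secondary results matter beyond this study, because Sample size says they will supply estimates of effect and variance and the information to size the next trial. Some of the analysis is discretionary as written: the summary statistic is open ("Numerical outcomes will be summarised using either mean (SD) or medians (IQR) as appropriate"), and Sensitivity and other planned analyses names six exploratory factors (donor type, chronic kidney disease, portal thrombosis, surgical approach, machine perfusion, site). A final report that called the analyst blinded would overstate the protection those choices had.

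**Working it through.** **Inputs from the protocol article:** N = 30 and arms of 20 and 10 (Sample size); ratio 2:1 (Randomisation); two labels (Allocation concealment); two strata by donor type (Randomisation).

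**Assumptions:** the article states no block scheme, so simple randomisation and permuted blocks of 3, 6, 9 and 12 were tried.

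**1. The plan's own figure.** 30 × 2/3 = 20 and 30 × 1/3 = 10. The stated arm sizes reproduce.

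**2. Simple randomisation.** Let X be the number on octreotide, X ~ Binomial(30, 2/3).

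- P(X > 15) = 0.957
- P(X = 15) = 0.025
- The guess that the larger group is octreotide, with a coin toss for a tie, is right with probability 0.957 + 0.025/2 = 0.969.

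**3. Permuted blocks in two donor strata.** Complete blocks hold exactly two thirds octreotide. The worst case puts every available placebo slot first in each stratum's unfinished block. The fewest octreotide patients possible at N = 30, over every split of the 30 between strata, are:

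| Block size | Fewest octreotide | Placebo |
|---|---|---|
| 3 | 19 | 11 |
| 6 | 18 | 12 |
| 9 | 18 | 12 |
| 12 | 16 | 14 |

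For blocks of 12, for example, 24 patients in two complete blocks give 16 octreotide. If the remaining 6 are all placebo, the split is 16 to 14. Octreotide is the larger group in every case, whatever the donor split. A simulation of 20,000 trials per block size, with an assumed 70:30 split of brain-death to cardiac-death donors, agreed: octreotide was larger in all of them.

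**4. Certainty from an observed split.** Under simple randomisation, with the two labels equally likely beforehand to mean octreotide, the probability that the larger group is octreotide is 1/(1 + 2^−d), where d is the difference in group size.

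- 20/10: d = 10, 1024/1025 = 99.9%
- 19/11: d = 8, 256/257 = 99.6%
- 17/13: d = 4, 16/17 = 94.1%

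**5. If recruitment falls short.** At N = 15, octreotide is the larger group with probability 91.2% under simple randomisation, and in 99.6% to 100% of simulated trials with blocks of 3 to 12.

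**The case against.** The arithmetic is hard to dispute. The case against concerns scope and consequence, and much of it stands.

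- **Timing.** The article does not say when the A/B variable reaches the statistician. Until labelled data are tabulated the statistician is blinded, and that may include the period in which the SAP is approved, since Statistical methods requires approval before analysis. A reader might infer that analyst blinding never exists. The text supports only that it fails once the labels are counted.
- **Data cleaning.** Because the code is broken after cleaning and analysis, a reader might infer that cleaning is done by someone who in effect knows the arms. The article does not give cleaning to the statistician or say that labels are present during it. Data collection assigns checks, queries and database lock to a separate data management procedure that is not shown.
- **Event classification.** A reader might also infer that borderline kidney injury or drug-relatedness calls could be shifted. No section gives those calls to the statistician. Kidney injury follows set creatinine and urine-output criteria. Clinicians and outcome assessors are protected by identical coded syringes and an off-site list, which group size in the statistician's dataset does not touch.
- **Mean or median.** This choice is ordinary SAP content and may be settled there. It is no fault by itself.
- **Small consequence.** The primary outcomes are feasibility counts and percentages with exact intervals, most of which do not depend on arm. There are no formal tests and no interim analysis.

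What the objection does not remove is the mismatch between the protection claimed and the means given. That is a stated property, not a detail left to another document.

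**Conclusion.** The point holds in a limited form. From the moment labelled data are tabulated, A/B coding alone does not blind the analyst, although Trial design and Allocation concealment say blinding lasts until analysis is complete. The arms can be told apart with probability about 96% to 97% under simple randomisation, and with certainty at 30 patients under stratified permuted blocks of 3 to 12. Block size is assumed, but the conclusion is the same across the range tried.

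The exposure is confined to choices the analyst makes in the descriptive secondary summaries and exploratory subgroups, and a detailed SAP would narrow it further. It does not reach patients, clinicians, outcome assessors or most of the primary feasibility counts. The correction is still worth making because it is nearly free and those secondary summaries are meant to inform the size of the next trial.

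**What to change.** Use one or both of the following.

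1. **Withhold the treatment column until database lock and SAP sign-off.** Settle remaining data decisions and finalise the analysis code before then, on pooled data or dummy allocations. After release the analyst should be regarded as able to identify the arms.
2. **Release three codes of about 10 patients each**, by splitting the octreotide arm at random into two. Group size then says little about which code is placebo. The analyst prepares each one-versus-two comparison, and the code break shows which applies.

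Then reword Trial design and Allocation concealment so that they claim analyst blinding only as far as the chosen method gives it. Under option 1 alone, that means saying that data decisions were made without treatment labels and that the analyst could identify the arms after lock.

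The cost is an instruction to the randomisation provider, slightly more programming, and a less favourable blinding statement. Treatment, recruitment and sample size do not change.
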